## Abstract

**Background:**

Hand eczema is a prevalent dermatological condition that significantly impacts the quality of life of affected individuals. Topical corticosteroids, such as Clobetasol Propionate, are commonly employed for management, but concerns regarding long-term use and potential side effects necessitate exploration of alternative treatments. This study protocol outlines a randomized controlled trial comparing the efficacy of topical Tofacitinib 2% ointment with Clobetasol Propionate 0.05% ointment in managing hand eczema.

**Methods:**

The study will be a single-blinded, parallel-group, randomized controlled trial conducted at the Dermatology outpatient department of Acharya Vinoba Bhave Rural Hospital Sawangi Meghe, Wardha, from March 2023 to September 2025. Eligible participants diagnosed with hand eczema will be randomized into two groups: Group 1 will receive Clobetasol Propionate 0.05% ointment, and Group 2 will receive Tofacitinib 2% ointment. The primary outcome measure is the change from baseline in the Hand Eczema Severity Index (HECSI) score, assessed at two weeks and four weeks. Statistical analysis will utilize appropriate parametric and non-parametric tests, with a p-value <0.05 considered significant.

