### Interventions

**Group 1 (Control): Topical Clobetasol Propionate 0.05% Ointment.** Patients in this group will receive topical Clobetasol Propionate 0.05% ointment as their treatment modality for hand eczema. They will be instructed to apply the ointment twice daily over the affected areas. The treatment duration will extend for 4 weeks.

**Group 2 (Experimental): Topical Tofacitinib 2% Ointment.** Patients in this group will receive topical Tofacitinib 2% ointment as their treatment modality for hand eczema. Similar to Group 1, they will be instructed to apply the ointment twice daily over the affected areas. The treatment duration will also be 4 weeks.

**Application instructions:** Patients in both groups will be educated on properly applying the assigned ointments. They will be instructed to wash their hands before applying a thin layer of the ointment evenly on the affected areas, avoiding contact with eyes and mucous membranes. Patients will be advised not to bandage or cover the treated areas unless directed by the investigator. Additionally, they will be instructed to avoid excessive sun exposure and use sunscreen on treated areas.

**Follow-up visits:** Participants from both groups will be scheduled for followup visits at 2 weeks and 4 weeks after the initiation of treatment. During these visits, clinical photographs will be taken with the patient’s informed consent, and the Hand Eczema Severity Index (HECSI)
^
5
^ score will be recorded to assess the efficacy and side effects of the respective interventions.

**Monitoring:** The study will be monitored to ensure adherence to the assigned interventions, proper data collection, and participant safety. Adverse events, if any, will be documented and reported. Regular communication with participants will be maintained to address any concerns or queries they may have during the study.

**Adjustments:** Any deviations from the study protocol will be documented, and appropriate measures will be taken to address them. Adjustments will be made in consultation with the Institutional Ethics Committee if necessary.

**Blinding:** The study will be single-blinded, with the participants unaware of their assigned treatment group. This helps minimize bias in reporting outcomes.

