### Sample size

Effect of topical tofacitinib for hand eczema = 81.7%

Effect of topical steroid for hand eczema = 68%

Clinically significant at (δ) = 25%

$$N={\left(1.64+0.84\right)}^{2}*\left(0.817\right)\;\left(1–0.817\right)+0.68\;\left(1-0.68\right)/{\left(0.25\right)}^{2}=36$$

Sample size = 36

Total sample size = 72 (36 per group)

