### Statistical analysis

The statistical analysis for this comparative study between topical Tofacitinib 2% ointment and topical Clobetasol Propionate 0.05% ointment in managing hand eczema will encompass a comprehensive approach utilizing appropriate parametric and non-parametric tests. The primary focus will be on the change from the baseline of the Hand Eczema Severity Index (HECSI) score. In the initial stage, descriptive statistics will be employed to summarize the baseline characteristics of participants in both treatment groups. Continuous variables will be presented as mean and standard deviation (or median and interquartile range), while categorical variables will be expressed as frequencies with percentages.

The comparative analysis will be conducted using an independent t-test or Mann-Whitney U test for the primary outcome—change from baseline in HECSI score. The choice between tests will depend on the data distribution, and statistical significance will be determined with a threshold of p<0.05. After the primary analysis, subgroup analyses may be undertaken to explore potential variations in treatment response based on age, gender, and baseline severity. Safety and adverse events will be summarized, and the incidence rates between the two treatment groups will be compared using Chi-square or Fisher’s exact test.

The handling of missing data will be addressed, potentially utilizing multiple imputations to enhance the robustness of the results. Sensitivity analyses may be performed to assess the impact of outliers or influential data points on the overall findings.

Exploratory analyses will investigate potential relationships between treatment response and additional factors, such as patient demographics or specific characteristics of hand eczema. Statistical software such as R Studio Version 4.3.1 will execute these analyses.

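### The primary outcome is placed at both week 2 and week 4 and the deciding visit is not named; if either visit could count, the false-positive risk would be roughly 7 to 9%

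*Protocol article*

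**What the plan says.** The abstract (Methods) gives the primary outcome as "change from baseline in the Hand Eczema Severity Index (HECSI) score, assessed at two weeks and four weeks", "with a p-value <0.05 considered significant". The Interventions section schedules "followup visits at 2 weeks and 4 weeks after the initiation of treatment" and has HECSI recorded at each visit; treatment lasts 4 weeks in both groups.

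The Statistical analysis section states: "The comparative analysis will be conducted using an independent t-test or Mann-Whitney U test for the primary outcome". It repeats that the outcome is change from baseline in HECSI, adds that "statistical significance will be determined with a threshold of p<0.05", and mentions no visit.

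The other sections do not settle it. The Sample size section works from two percentages, "Effect of topical tofacitinib for hand eczema = 81.7" and "Effect of topical steroid for hand eczema = 68", and attaches neither to a visit. The Discussion again calls HECSI the primary outcome measure without a time point.

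**The concern.** The time point is part of the definition of a primary endpoint. Here the outcome carries two time points, while the named tests (independent t-test or Mann-Whitney) compare two groups on one change score per patient. Applied to this outcome, they can give a week-2 result and a week-4 result, each measured against the same 0.05 threshold.

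Two things are at stake. First, the visit reported as primary could be chosen after the data are seen, which raises the chance of a false-positive conclusion. Second, if one visit is significant and the other is not, the protocol cannot say whether the trial met its primary objective. The second problem exists whatever the correlation between visits.

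**Working it through.** **What the plan's own figure covers.** The protocol gives no overall type I error beyond the 0.05 threshold. The only figure to reproduce is the sample size, reading the printed formula with brackets around the variance sum:

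- (1.64 + 0.84)² = 6.1504
- 0.817 × 0.183 + 0.68 × 0.32 = 0.1495 + 0.2176 = 0.3671
- 6.1504 × 0.3671 / 0.25² = 36.1, which matches the stated 36 per group

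The calculation allows for a single comparison of two rates and refers to no visit, so it does not show which visit was meant. The 1.64 is the one-sided 5% normal value; the analysis section does not state sidedness.

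**Inputs for the error calculation.** From the protocol: two post-baseline visits, a two-sample test of a change score, and a 0.05 threshold. Assumed: each visit is tested separately, significance at either is success, and the two test statistics have correlation ρ.

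**Formula.** With no true difference at either visit, and Z₂ and Z₄ the standardised statistics at weeks 2 and 4,

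P(at least one significant) = 1 − P(|Z₂| < 1.96 and |Z₄| < 1.96).

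At ρ = 0 this is 1 − 0.95² = 9.75%. Because each test has a 5% rate, P(exactly one significant) = 2 × P(at least one) − 10%.

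| Assumed ρ | At least one, two-sided | Exactly one, two-sided | At least one, one-sided 5% |
|---|---|---|---|
| 0.5 | 9.1% | 8.1% | 8.8% |
| 0.8 | 7.8% | 5.6% | 7.5% |
| 0.9 | 7.0% | 4.1% | 6.8% |

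Simulated two-sided t-tests with 36 per group (40,000 runs) gave 9.0% at ρ = 0.5 and 7.5% at ρ = 0.8, in line with the table apart from simulation error.

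**Why 0.5 to 0.9.** Both change scores subtract the same baseline. With equal variances and pairwise correlations r₀₂, r₀₄ and r₂₄ between baseline, week 2 and week 4, the two changes correlate at

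(1 + r₂₄ − r₀₂ − r₀₄) / √[(2 − 2r₀₂)(2 − 2r₀₄)].

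If all three correlations equal r, this is (1 − r) / (2 − 2r) = 0.5, whatever r is. If the two treated visits resemble each other more than they resemble baseline, it is higher: r₀₂ = 0.6, r₀₄ = 0.5, r₂₄ = 0.7 gives 0.67, and 0.6, 0.4, 0.8 gives 0.82. These are illustrations; the protocol reports no such correlations.

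**The case against.** A reader might infer that the trial has two primary tests, each at 5%, that either can be called success, and that the error rate is therefore 8 to 9.5%. The protocol does not support that as a statement of fact:

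- It nowhere says that the visits are tested separately. The analysis section describes one comparison, and the abstract's wording could be read as a measurement schedule.
- It gives no success rule. If both visits had to be significant, or only week 4 counted, there would be no inflation.
- The 9.5% needs a correlation of about 0.3, which is hard to defend when both changes share a baseline.

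It can also be said that this is a condensed article, and that a fixed sequence, an alpha split or a descriptive role for week 2 is commonly left to the analysis plan. That is fair, and the absence of a multiplicity procedure is not itself the point here.

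These objections limit the size of the problem but do not remove it. The article does state its primary outcome, with two time points and one threshold, and no section says which one decides. A measurement schedule would still leave the primary visit unnamed.

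**Conclusion.** The point holds as an undefined deciding visit. That conclusion rests on the text alone: two time points in the primary outcome, one threshold, and no rule linking them.

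The inflation is conditional. It requires separate 5% tests and success at either visit. On those terms the false-positive risk is roughly 7 to 9% instead of 5%, for an assumed correlation of 0.9 down to 0.5. One-sided tests give slightly lower figures, 6.8 to 8.8%, and the same conclusion. Any extra error from choosing between the t-test and the Mann-Whitney test on the data is not counted.

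The Study status section says the trial has not started, so the visit can still be fixed before any outcome is known.

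**What to change.** In both the abstract and the Statistical analysis section, name change in HECSI from baseline to week 4, the end of the 4-week treatment, as the single primary endpoint, tested at the trial's 0.05 level. Make week 2 secondary: either tested only if week 4 is significant, or reported descriptively. This gives the trial one defined primary result and keeps the error from having two visits at or below 5%.

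Sidedness should be settled separately and made consistent with the 1.64 in the sample size; naming the visit does not decide it.

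The change is a sentence in each of the two places and alters neither the visits nor the number of patients. The downside is that a difference seen only at week 2 could no longer support a primary claim.

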**Expected Outcome:**

The study is anticipated to provide insights into the comparative efficacy and safety of Tofacitinib and Clobetasol Propionate in managing hand eczema. A favorable outcome for Tofacitinib could suggest its potential as an alternative or adjunctive therapy, offering a more targeted approach with fewer side effects. The findings may contribute to optimized treatment strategies for hand eczema, improving patient outcomes and guiding future research in dermatological therapeutics.

## Introduction

Hand eczema is a common dermatological condition characterized by inflammation of the skin on the hands, leading to symptoms such as erythema, vesicles, fissures, and pruritus.
^
1
^ It significantly impacts the quality of life of affected individuals, causing discomfort and functional impairment.
^
2
^ The management of hand eczema often involves topical corticosteroids, with Clobetasol Propionate being a commonly prescribed agent.
^
3
^ However, concerns regarding the long-term use of potent corticosteroids, potential side effects, and the need for alternative treatments have prompted exploration into novel therapeutic options.

One emerging candidate for managing inflammatory skin conditions is Tofacitinib, a Janus kinase (JAK) inhibitor that modulates cytokine signaling and has demonstrated efficacy in conditions like psoriasis.
^
4
^ Tofacitinib’s mechanism of action, targeting critical pathways involved in skin inflammation, makes it a promising candidate for hand eczema management.

While studies have explored the efficacy of topical corticosteroids like Clobetasol Propionate in hand eczema, there needs to be more comparative research evaluating the potential advantages of Tofacitinib over traditional treatments. This study seeks to address this gap by conducting a randomized controlled trial comparing the efficacy and safety of topical Tofacitinib 2% ointment with topical Clobetasol Propionate 0.05% ointment in managing hand eczema.

### Aim

To study the efficiency of topically applied tofacitinib 2% ointment in managing hand eczema.

### Objectives

1.To evaluate the efficacy of topical tofacitinib 2% ointment in hand eczema.2.To evaluate the efficacy of topically applied clobetasol propionate 0.05% ointment for hand eczema.3.To compare the effect of topically applied tofacitinib 2% ointment and topically applied clobetasol propionate 0.05% ointment in hand eczema.4.To study the side effects of topical clobetasol propionate 0.05% ointment and topical Tofacitinib 2% ointment.

## Protocol

### Study design

This research will be conducted as a prospective, randomized, single-blinded, parallel-group, controlled trial to compare the efficacy of topical tofacitinib 2% ointment versus topical clobetasol propionate 0.05% (10-15 g depending on the area affected over 4 weeks Reagent number: 25122-46-7) ointment in the management of hand eczema.

### Participants

Patients diagnosed with hand eczema attending the outpatient department of Dermatology (DVL) at AVBRH Sawangi Meghe, Wardha, from March 2023 to September 2025, will be eligible for participation.

### Inclusion criteria

1.Patients providing written consent before the initiation of any treatment.2.Clinically diagnosed cases of hand eczema of all grades as per the Hand Eczema Severity Index (HECSI) score.3.Age above 18 years.4.No prior treatment for hand eczema in the past 1 month.

### Exclusion criteria

1.Patients with an active infection at the local site.2.Patients with leukopenia or anemia.3.Pregnant or nursing women.4.Patients on any treatment that may influence the outcomes of the drugs under study.

### Allocation

Patients meeting the inclusion criteria and providing written consent will be assigned to either Group 1 or Group 2 using computer-generated randomization. To minimize bias, age, and gender cross-matching between the groups will be implemented.

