### Enrollment

1.
**Recruitment:** The recruitment process will commence at the Dermatology outpatient department (DVL) of AVBRH Sawangi Meghe, Wardha, from March 2023. A designated study coordinator will identify potential participants based on clinical diagnosis and eligibility criteria. Eligible patients will be provided with detailed information about the study, and the purpose, risks, and benefits will be explained.2.
**Informed consent:** Written and signed informed consent will be obtained from all eligible patients willing to participate in the study. The consent form will include information about the nature of the study, potential risks and benefits, confidentiality assurances, and the voluntary nature of participation.3.
**Screening and inclusion/exclusion criteria:** Eligible participants will undergo a screening process to confirm their clinical diagnosis and ensure they meet the inclusion criteria while excluding those who meet any exclusion criteria. The study coordinator will collect relevant medical history and conduct a thorough examination to confirm the diagnosis of hand eczema.4.
**Baseline assessments:** Baseline assessments will include the collection of demographic information, medical history, and baseline Hand Eczema Severity Index (HECSI) scores. Clinical photographs of affected areas will be taken during followup visits for documentation and comparison.5.
**Randomization and allocation:** After obtaining informed consent and confirming eligibility, participants will be assigned to either Group 1 (Clobetasol Propionate) or Group 2 (Tofacitinib) through computer-generated randomization. Age and gender cross-matching will be performed to ensure balanced groups.6.
**Assignment of interventions:** Participants will be provided with the assigned treatment (topical Clobetasol Propionate 0.05% ointment or topical Tofacitinib 2% ointment) along with detailed instructions for application.7.
**Follow-up appointments:** Participants will be scheduled for followup visits at 2 weeks and 4 weeks after the initiation of treatment. The study coordinator will communicate the importance of attending all followup appointments and the need for adherence to the assigned treatment.8.
**Monitoring adherence:** Adherence to the assigned intervention will be monitored through self-reporting, return of unused medications, and documentation during followup visits.9.

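### An undefined age and gender cross-matching step is added to computer randomisation; it leaves room for non-random or predictable assignment, and the primary test does not account for it

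*Protocol article*

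**What the plan says.** The Allocation section states that eligible, consenting patients "will be assigned to either Group 1 or Group 2 using computer-generated randomization". The next sentence adds a second operation: "To minimize bias, age, and gender cross-matching between the groups will be implemented". The Enrollment section, in its item on randomisation and allocation, repeats both and gives balance as the purpose: "Age and gender cross-matching will be performed to ensure balanced groups". Neither section says whether this means stratification, minimisation, pair matching or something done by staff.

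On who could know what, the Enrollment section says "A designated study coordinator will identify potential participants based on clinical diagnosis and eligibility criteria"; the same coordinator takes the history and examines patients at screening. The blinding paragraph under Interventions reads "The study will be single-blinded, with the participants unaware of their assigned treatment group" and does not mention staff or assessors.

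For the analysis: "The comparative analysis will be conducted using an independent t-test or Mann-Whitney U test for the primary outcome", the outcome being change from baseline in HECSI. Age and gender appear in the Statistical analysis section only as possible subgroup factors ("subgroup analyses may be undertaken to explore potential variations in treatment response based on age, gender, and baseline severity"), and demographics appear again in exploratory work. Neither adjusts the primary comparison.

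**The concern.** Matching between groups belongs to observational designs. A simple computer sequence balances age and gender only in expectation, so it cannot guarantee matched groups among 72 patients. Something more is needed. It can be built into the computer sequence, or it can be a person choosing or placing patients according to who is already in the other arm. The text allows either.

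If it is the second, the assignments concerned are no longer random. Anyone who knows earlier allocations and the matching rule could then foresee the next arm and influence who is enrolled. A step introduced to reduce bias would open a route for selection bias, and no later analysis can repair that reliably.

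There is also a smaller mismatch. If the arms really are balanced on age and gender by design, a test for two unrelated samples ignores that design.

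**Working it through.** **1. The plan's own figure.** The Sample size section gives 36 per group. With the variance sum bracketed:

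n = (1.64 + 0.84)² × [0.817 × 0.183 + 0.68 × 0.32] / 0.25² = 6.1504 × 0.367111 / 0.0625 = 36.13.

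This reproduces 36 per group and 72 in total. The calculation does not involve matching, so the present point does not change it.

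**2. What the wording permits.**

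- *Computer-run stratification or minimisation with concealment:* compatible with the randomisation sentence. Predictability is small or absent.
- *Sequential pairs, first member randomised:* the second member's arm is fixed by the first.
- *Staff selecting or placing patients to match:* assignment is not random for those patients.

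The protocol does not say which applies.

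**3. Size of the predictability under sequential pairs.** Conditions: matching is in pairs, pairs are filled one after the other, and the first member's arm is known to those recruiting.

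- Pairs: 72 / 2 = 36, so 36 assignments (50%) are determined.
- Correct guesses: 36 known + half of the other 36 = 36 + 18 = 54, and 54 / 72 = 75%, against 50% under simple randomisation.

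If any of the three conditions fails, these figures do not apply.

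**4. Effect on the primary test.** Let R² be the share of the variance of HECSI change explained by the matched factors. The documents do not give it, so a range is shown. When the arms are matched on those factors, the unadjusted standard error exceeds the correct one by the factor 1/√(1 − R²):

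- R² = 0.05: 1/√0.95 = 1.026
- R² = 0.10: 1/√0.90 = 1.054
- R² = 0.20: 1/√0.80 = 1.118

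A simulation of 36 matched pairs (20,000 runs per setting, nominal two-sided 0.05, normal outcome) compared the independent t-test with a paired t-test. The 0.66 SD difference used for power is an assumption.

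| R² (assumed) | Type I error, independent t-test | Power, independent | Power, paired |
|---|---|---|---|
| 0 | 0.051 | 0.79 | 0.78 |
| 0.05 | 0.046 | 0.79 | 0.80 |
| 0.10 | 0.036 | 0.80 | 0.81 |
| 0.20 | 0.028 | 0.82 | 0.86 |
| 0.30 | 0.020 | 0.83 | 0.90 |
| 0.50 | 0.007 | 0.86 | 0.97 |

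The independent test errs on the safe side. Its type I error falls below 0.05 as R² rises, and it gives up some power. At R² of 0.05 or less the difference is negligible.

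**The case against.** The strongest reply is that cross-matching is loose wording for a legitimate method. Balancing age and gender is compatible with computer randomisation through stratification, minimisation or randomisation within pairs. The Enrollment section places the phrase inside the randomisation step, with balance as its aim. No section describes anyone placing or reassigning a patient. All of this stands. A reader might infer that the protocol overrides its own randomisation and that selection bias is therefore present; the documents do not support that.

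Nor do they establish that staff know earlier allocations. The blinding paragraph is silent about staff. The code-break paragraph gives the treating physician access to the allocation in an emergency, which suggests that this physician does not routinely hold it. The absence of concealment detail is not a fault in itself, because a journal article commonly leaves that to the full protocol. The figure of 36 of 72 is therefore a worst case under stated conditions.

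A reader might also infer that baseline severity is left unbalanced because it is not a matching factor. It is not: valid randomisation balances it in expectation, and the outcome is a change from baseline. Stratifying by severity is a design preference.

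On the analysis, the plan does not disregard age and gender altogether, since they appear in the optional subgroup work. For the primary test the cost is efficiency only.

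What the reply does not remove is that the article states a matching step twice, separately from the computer randomisation, in words that a site could carry out by hand.

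**Conclusion.** The point holds in a conditional form. The protocol adds to its randomisation a step that is not a recognised randomisation procedure, and one natural way of carrying it out would make assignments non-random or predictable. In the worst case, sequential pairs with the first arm known, half of the assignments (36 of 72) would be determined. Under a concealed computer-run stratified or minimised scheme the risk would be small or nil. The documents do not show which was meant.

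The mismatch with the primary test is minor. It makes the test conservative, with a standard error about 5 to 12% too wide at an assumed R² of 0.10 to 0.20, and it matters little at 0.05 or less. It does not bias the comparison or raise the false-positive rate.

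The allocation part is the reason to act before enrolment; the analysis part alone would not be pressing.

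**What to change.** Before the first patient is randomised:

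1. Delete the cross-matching sentences in the Allocation section and in the randomisation item of the Enrollment section.
2. State in their place that balance comes from a pre-generated computer sequence, concealed from those who recruit until the patient is enrolled, and stratified or minimised with a random element on gender and age band. State that staff neither select nor reassign patients to achieve balance.
3. Analyse the primary outcome by ANCOVA of HECSI with baseline HECSI, age and gender as covariates. Baseline HECSI is already collected, so this needs no new data. Once baseline is in the model, the treatment estimate is the same whether the response is the follow-up score or the change.

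Stratifying by a baseline HECSI band as well is optional.

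The cost is low. The Study status section says that the trial has not started, so the change is a randomisation list and a few sentences. Exact age matching is given up, and the primary analysis becomes slightly more complex.

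### Baseline HECSI is controlled neither at allocation, which balances only age and gender, nor in the unadjusted primary test, which costs precision and leaves chance severity differences uncorrected.

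*Protocol article*

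**What the plan says.** The Allocation section assigns patients by computer-generated randomisation and adds: "To minimize bias, age, and gender cross-matching between the groups will be implemented". Item 5 of the Enrollment section repeats it: "Age and gender cross-matching will be performed to ensure balanced groups". No other balancing factor is named.

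The severity range is wide. The Inclusion criteria admit "Clinically diagnosed cases of hand eczema of all grades as per the Hand Eczema Severity Index (HECSI) score". Item 4 of the Enrollment section provides for the score: "Baseline assessments will include the collection of demographic information, medical history, and baseline Hand Eczema Severity Index (HECSI) scores". Randomisation is item 5, so the score should be in hand when a patient is assigned. That rests on the order of the items, as no sentence says it outright.

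The abstract's Methods paragraph defines the endpoint: "The primary outcome measure is the change from baseline in the Hand Eczema Severity Index (HECSI) score, assessed at two weeks and four weeks". The Statistical analysis section compares it by "independent t-test or Mann-Whitney U test for the primary outcome", with the choice depending on the distribution. Baseline severity enters the analysis in one place only: "subgroup analyses may be undertaken to explore potential variations in treatment response based on age, gender, and baseline severity".

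**The concern.** Baseline HECSI is part of the endpoint. A patient cannot lose more points than he or she starts with, so an arm that happens to receive more severe cases will tend to show the larger mean fall, whatever the drugs do. The plan balances two factors that the document does not link to HECSI change, and leaves out the one factor that is arithmetically tied to it. The planned test does not make up for this, because it compares raw changes without using baseline.

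At stake are the precision of a comparison with 36 patients per arm and the credibility of its result if the arms differ visibly in severity at the start. The optional severity subgroups could also be uneven between arms.

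**Working it through.** **Arm size.** The plan's figure reproduces once brackets are put round the variance sum: (1.64 + 0.84)² × [0.817 × 0.183 + 0.68 × 0.32] / 0.25² = 36.13, stated as 36 per group. It is used here only as the arm size.

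**Chance imbalance.** If allocation ignores HECSI, the standardised difference in mean baseline has SE √(2/36) = 0.236 SD, so its 95% chance range is ±1.96 × 0.236 = ±0.46 SD. From 2 × [1 − Φ(d/0.236)]:
- above 0.25 SD: 29%
- above 0.4 SD: 9%
- above 0.5 SD: 3.4%

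This step uses a normal approximation and needs no assumption about the spread of HECSI.

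**Effect on the planned contrast.** The documents give no HECSI SD and no correlation between baseline and follow-up. Assume equal SDs at both times and a correlation ρ of 0.3 to 0.7. Given a baseline difference of d SD, the unadjusted difference in change shifts by (1 − ρ)d. The variance per patient is 2(1 − ρ) for the change score and 1 − ρ² after adjustment for baseline, a ratio of (1 + ρ)/2.

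| ρ | Shift at d = 0.25 | Shift at d = 0.5 | Variance, adjusted / unadjusted |
|---|---|---|---|
| 0.3 | 0.175 SD | 0.35 SD | 0.91/1.40 = 0.65 |
| 0.5 | 0.125 SD | 0.25 SD | 0.75/1.00 = 0.75 |
| 0.7 | 0.075 SD | 0.15 SD | 0.51/0.60 = 0.85 |

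The false-positive rate in trials with a given imbalance stays at about 5% for d = 0.25. For d = 0.5 it is 19% (ρ = 0.3), 15% (0.5) or 11% (0.7).

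**Simulation with a proportional response.** Assumptions: log-normal baseline HECSI, the same mean 70% reduction in both arms, SD of individual reduction 0.2, 36 per arm, 2,500 trials per setting. The SD of the arm difference in change is in HECSI points. Its level depends on the assumed average score, so only the ratios matter.

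| Design and analysis | Log SD 0.5 | 0.7 | 0.9 |
|---|---|---|---|
| Unstratified, unadjusted (as planned) | 3.51 | 5.39 | 8.73 |
| Three bands, unadjusted | 2.46 | 3.94 | 6.83 |
| Unstratified, baseline-adjusted | 1.73 | 2.12 | 2.76 |
| Three bands, baseline-adjusted | 1.69 | 2.07 | 2.66 |

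- Three bands alone cut the variance by 1 − (2.46/3.51)² = 51%, 1 − (3.94/5.39)² = 47% and 1 − (6.83/8.73)² = 39%.
- Adjustment alone cuts it by 1 − (1.73/3.51)² = 76%, 1 − (2.12/5.39)² = 85% and 1 − (2.76/8.73)² = 90%.
- Adding bands to an adjusted analysis lowers the SD by only a further 2% to 4% (1.69/1.73, 2.07/2.12, 2.66/2.76).
- Mean baseline differs by 20% or more in 16%, 31% and 47% of unstratified trials, against 2%, 13% and 31% with three bands.
- Type I error without stratification is 3.9% to 4.9% for the t-test and 4.3% to 5.4% for Mann-Whitney. With three bands and the same unadjusted tests it falls to 0.4% or less. The tests ignore the stratification, so their standard errors are too large.

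**The case against.** Randomising without stratifying on severity is valid, and the protocol makes no error or self-contradiction here. A reader might infer that leaving HECSI out of allocation biases the trial or raises its false-positive rate. The documents do not support that: under randomisation, chance imbalance averages to zero, the planned test's standard error already allows for it, and the simulated type I error stays near 5%. This part of the objection stands in full.

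It also stands that allocation is the weaker lever. Baseline adjustment alone gains more than three bands do, and once baseline is in the model, bands add little precision. A stratified list without a matching analysis would make the planned test far too conservative, so a new list on its own is not a remedy.

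A reader might further infer that age and gender should give way to HECSI. Nothing in the document shows that balancing them does harm, and the Statistical analysis section names both as subgroup factors beside baseline severity.

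Finally, an unseen analysis plan could add baseline adjustment. But the protocol does not leave the point open: it names its balancing factors and its primary test, and baseline HECSI is in neither. What remains is avoidable imprecision and exposure to chance imbalance in the single trial that is run.

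**Conclusion.** The point holds as a recommended improvement in efficiency and robustness. It is not a finding of bias. Neither allocation nor the primary analysis uses baseline HECSI, although it should be available before assignment and forms part of the endpoint.

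The chance of an imbalance above 0.25 SD is about 29%. An imbalance of that size shifts the estimate by 0.075 to 0.175 baseline SD but leaves the false-positive rate near 5%. Imbalance large enough to mislead a test seriously, above 0.5 SD, is uncommon at 3.4%.

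The gain from baseline adjustment depends on assumptions that the documents cannot settle. It is 15% to 35% of the variance with equal SDs and ρ of 0.3 to 0.7, and 76% to 90% if falls are proportional to a skewed baseline. The direction is the same under both sets of assumptions.

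**What to change.** 1. In the Statistical analysis section, make the primary analysis of HECSI change a linear model with treatment and continuous baseline HECSI. This gives most of the precision gain and needs no extra data.
2. In the Allocation section and Enrollment item 5, add baseline HECSI, in two or three pre-set bands, as a stratification factor of the computer-generated list. Use concealed, varying block sizes. State that the score is entered before the assignment is released.
3. If the list is stratified, require the primary analysis to include the band or baseline HECSI. Do not combine a stratified list with the unadjusted test.
4. Leave age and gender as they are, or make them covariates.

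The Study status section says that the trial has not begun, so the cost is a new list and a revised analysis paragraph, with no added patients, visits or measurements. There are small downsides. The document gives no severity cut-offs, so these must be fixed in advance. Only participants are blinded, and with 72 patients over two or three bands (about 36 or 24 each if equal), staff could guess late assignments slightly more easily. Varying block sizes limit that. If stratifying proves impractical, step 1 alone is still worth making.
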